## Abstract

**Background:**

Effective preventative interventions are urgently needed to address the increasing rates of e-cigarette use among young people and to complement the Australian government’s latest tobacco control measures. School-based interventions using peer leaders can effectively shape social norms and expectations associated with tobacco use. This paper describes the protocol for the Breathe Easy All Together (BEAT) study, a process and impact evaluation of the first school-based peer-leadership intervention to prevent adolescent e-cigarette use in Australia.

**Methods:**

A pre-post test design will be used to conduct process and impact evaluation of the BEAT program using the RE-AIM (Reach, Effectiveness, Adoption, Implementation and Maintenance) framework. The intervention utilises a multi-component peer-education model driven by students, to promote respiratory health and resist e-cigarette use within a supportive school environment. Volunteer Year 10 students (14- to 16-years-old) will be trained by the research team as peer leaders, to deliver two 60-min lessons to Year 7 students (11- to 13-years-old) during routine health education classes. Year 10 peer leaders and Year 7 students will complete online self-report surveys pre- and post-program to assess changes in the primary outcome of past-30-day e-cigarette use. Secondary outcomes include tobacco use behaviours, e-cigarette knowledge, perceptions, refusal skills, intentions to use e-cigarettes, and acceptability of intervention components. School staff involved in the delivery of the program will participate in semi-structured interviews to examine acceptability and factors affecting program implementation. Descriptive statistics and changes between data collection points will be assessed using Wilcoxon signed rank tests to investigate intervention effect on primary and secondary outcomes. Qualitative data will be analysed in alignment with RE-AIM constructs using Framework Analysis.

**Discussion:**

Building upon an evidence-based peer-education model, BEAT presents a novel peer-led solution to address a gap in current research practice to prevent adolescent e-cigarette use in Australia. It has the potential to protect the future health and wellbeing of students from the harms of e-cigarette use and nicotine addiction. The RE-AIM framework is a comprehensive approach to conducting robust evaluation of multi-faceted interventions in the school environment. If effective, funding support will be sought for wider dissemination and further evaluation.

## Background

In recent years, the use of e-cigarettes (or ‘vaping’) has rapidly increased among young people, particularly among those who do not smoke. Global trends indicate the prevalence of e-cigarette ever use among young people (aged < 20 years) to be over 40% in high income countries, including the United States, France, Italy and Spain [1]. In a national survey of current smoking and vaping patterns across Australia, past 30-day e-cigarette use in adolescents aged 14—17 years has increased from 0.8% in 2018 to 14.5% in 2023 [2]. This rapid increase in adolescent e-cigarette use has been fuelled by several factors, including appealing flavours, social pressures, curiosity, targeted industry marketing, and misperceptions of e-cigarette use as safer than smoking [3].

Although e-cigarettes were originally designed as safer nicotine delivery systems for adult smokers, disposable e-cigarettes have gained popularity among young people who have never smoked [4, 5]. While the evidence for the health effects of e-cigarette use is limited and varies in strength, Banks et al.’s systematic review has shown e-cigarette use causes a range of acute cardiac and respiratory problems, including e-cigarette or vaping use-associated lung injury (EVALI), seizures, poisoning, burns and nicotine addiction [6]. Nicotine use in adolescence can lead to impaired brain development and worsened mental health outcomes, such as depression and substance abuse disorders [7]. Importantly, young people who use e-cigarettes are three times more likely to initiate tobacco smoking compared to those who do not use e-cigarettes [8].

In Australia, the purchase and sale of nicotine e-cigarette products to people aged under 18 years is illegal [9]. Despite this, regulatory gaps prior to 2024 have allowed nicotine e-cigarette products to become easily accessible to young people through retailers, tobacconists, convenience store, social media, and friends and family [5]. In response, in July 2024, the Australian Federal Government has implemented a suite of rapidly evolving regulatory and non-regulatory measures to quash the black-market and protect young people from the health risks of e-cigarette use [9]. While these regulatory changes predominantly focus on restricting the supply of e-cigarettes, other measures include significant investment in lung cancer screening, Tackling Indigenous Smoking, public health information campaigns, and smoking and vaping cessation support [10]. These measures will likely take months to years to have a broader effect on the e-cigarette market in Australia, and in the interim, e-cigarettes remain readily accessible and frequently used among young people. Thus it is critical that preventative interventions addressing the demand for tobacco and e-cigarette products are also implemented to empower young people with the knowledge, skills and confidence to resist and make informed choices about e-cigarette use [11]. Empowering young people may also motivate them to comply with the latest e-cigarette laws [12].

Schools are ideal settings for the delivery of preventative interventions as they provide access to a significant proportion of the adolescent population and can influence the establishment of health behaviours [13, 14]. Additionally, substance use prevention is a mandatory component of the personal development and health education curriculum in Australia [15]. Preventative interventions delivered in group or classroom settings can help adolescents make informed decisions about tobacco use while developing both self and collective efficacy [3, 16]. While there is mixed evidence for the effectiveness of school-based tobacco prevention programs, a systemic review and meta-analysis demonstrated strong evidence for multi-component interventions which integrate a combination of social competence and influence curricula [17]. Such programs have demonstrated a 12% reduction in the uptake of smoking compared to controls at 1 year follow-up [17]. Other components of successful tobacco prevention programs include the delivery of multiple sessions, interactive curricula, refusal skill practice, normative education, and use of peer leaders [3, 18, 19].

While numerous school-based e-cigarette prevention programs have emerged in recent years, informed by best practices in tobacco control, there is a paucity of evidence for their effectiveness. A 2024 systematic review of e-cigarette preventative interventions targeting children and adolescents found school-based interventions show mixed results in reducing the uptake, prevalence or intentions to use e-cigarettes [20]. Of 14 school-based interventions, only Above The Influence of Vaping (ATI-V) and INCLUSIVE were found to reduce the prevalence of e-cigarette use [21, 22]. One of two studies evaluating CATCH My Breath (CMB) reported a lower uptake of e-cigarette use compared to controls [23]. These interventions were aligned with best practices, delivering normative education with resistance and social skills training [20]. CMB and ATI-V also incorporated elements of peer-led programming [22, 23]. Most school-based programs effectively increased students’ knowledge and harm perceptions of e-cigarettes post intervention, although they produced no effect, increased, or decreased students’ intentions to use e-cigarettes [20]. Further research utilising robust evaluation methods is urgently required to identify effective components of e-cigarette prevention programs and the necessary conditions for successful implementation in the school context [3].

A systematic review of interventions aimed at children and adolescents [18] did not include any Australian interventions. There is currently one school-based eHealth e-cigarette prevention program, OurFutures, being evaluated in clustered randomised control trial in 42 secondary schools across Australia, with results still pending [24]. A range of effective, acceptable, and relevant school-based interventions are needed to complement government efforts to address increasing rates of e-cigarette use among young Australians.

In early 2021, the Prevention Education and Research Unit (PERU), Western Sydney Local Health District, initiated a community-led approach in response to local secondary schools’ appeals for help to address increasing rates of e-cigarette use among students, and the school-disruption associated with managing e-cigarette use. This approach is conducted in partnership with the New South Wales (NSW) Department of Education and Eastern Creek Principals Network with the aim to build the agency of school communities to reduce the initiation and use of e-cigarettes in students. Prior to the development or implementation of interventions to address student e-cigarette use, PERU conducted formative research to determine students, school staff, and parents’ perceptions of e-cigarette use and their preferred prevention strategies [25]. Informed by the findings this qualitative exploratory study, PERU developed the Breathe Easy All Together (BEAT) peer-leadership program, an adaptation of the Adolescent Asthma Action (Triple A) program, which has shown to be effective in improving asthma outcomes and resilience to tobacco initiation in Australia and internationally [26, 27]. BEAT complements the school curriculum and seeks to add value to the school community by providing students with an opportunity to be involved in the delivery of prevention messaging.

This research study seeks to conduct process and impact evaluation of the BEAT program, informed by the RE-AIM framework (reach, effectiveness, adoption, implementation and maintenance). The objectives of the study are to:determine the impact of the BEAT program on Year 7 and Year 10 students’ e-cigarette use, combustible cigarette use, intentions to use, knowledge, perceptions and refusal skills.explore the experience of Year 10 students as BEAT Peer Leaders in delivering the BEAT program.describe program reach and adoption across participating sites.identify barriers and facilitators affecting the implementation and ongoing maintenance of the BEAT program in school settings.

## Methods

### Participants

Eligible participants will be Year 10 students (aged 14—16 years) and Year 7 students (aged 11—13 years) attending participating secondary schools in NSW, Australia, between 2024 and 2025. Students may participate regardless of their smoking or e-cigarette use status. All students who do not opt-out of the study or are not opted-out by their parent/guardian, will automatically be entered into the study. School staff who are involved in the implementation of the BEAT program, including the BEAT program coordinator, will be eligible to participate. Schools receiving other e-cigarette prevention programs or are enrolled in trials testing such interventions (e.g. OurFutures and Reality Now) will be excluded.

### Intervention

The Breathe Easy All Together (BEAT) program is a multi-component peer-leadership program which aims to empower students by providing them with the knowledge, skills and confidence to make informed decisions about e-cigarette use and advocate for respiratory health (see Table 1). The BEAT program utilises an evidence-based peer-education model, driven by students, to promote respiratory health and resilience to e-cigarette use in a supportive school environment [27–29]. This model is underpinned by social cognitive theory and the empowerment education approach [30, 31]. Social Cognitive Theory centres on the concept of reciprocal determinism, where cognitive, behavioural and environmental factors interact to determine individual behaviour change [30]. The Empowerment Education Framework is an effective preventative health model in which people are empowered to take control over their lives as agents of social action within their communities [31]. Through education, participants are facilitated to determine their own priorities and the necessary actions to collectively affect environmental conditions. BEAT combines these methodologies to contribute to the creation of a supportive school environment in which students drive behavioural change through the delivery of normative education, peer role modelling, and social reinforcement.

**Table 1 Tab1:** Overview of the BEAT Program content

Intervention component	Activities and key messages
Online Course	The online course provides normative education on: Chemical contents of e-cigarette, consequences of e-cigarette use, reasons why young people do and do not use e-cigarettes, alternatives to e-cigarette use and industry marketing tricks and tactics
Peer leader workshop for Year 10 students	The students participate in a series of interactive activities based on empowerment education which include: Group Agreements, asthma first aid, empowerment activity, unpacking tobacco statements, peer pressure to use e-cigarettes, refusal skill practice, life hack lotto highlighting alternatives to e-cigarette use, coping skills race, unpacking an image and industry marketing tactics and BEAT Peer Leader practice
Peer-education lessons for Year 7 students	These include: Group Agreements, online course, empowerment activity, peer pressure and e-cigarette refusal skill practice and life hack lotto highlighting alternatives to e-cigarette use

Steps of the BEAT Program:

Online Course: Year 10 students (approximately 15—30 students per school) who have volunteered or been selected to participate in the BEAT program as a peer leadership opportunity, complete a 45-min online course. The online course developed by PERU, provides students with normative education regarding the contents of e-cigarettes, harms of use, alternatives to use, and industry marketing strategies.Peer Leader Workshop: The same group of Year 10 students participate in a one-day workshop held by the research team during school hours, where they receive education and engage in interactive activities to learn about asthma and what to do in an asthma emergency, resisting e-cigarette use, and acquiring skills in group facilitation (see Fig. 1). They practise being a BEAT Peer Leader, using a manual detailing the content of the peer-education lessons for Year 7 students.Peer Education Lessons: BEAT Peer Leaders, in teams of four students, deliver 2 × 60-min lessons to Year 7 students during routine personal development and health education. The lessons include facilitation of the online course, followed by interactive activities and a game to reinforce learning. A classroom teacher will be present to assist with classroom management, and a member of the research team will be present to monitor intervention fidelity.

**Fig. 1 Fig1:**
[figure not shown]
Example of video shown during the empowerment activity for Year 10 and 7 students

### Pilot testing

The BEAT program was piloted in four public secondary schools with 90 students to ensure its feasibility and acceptability. The formative evaluation was underpinned by an Action Research approach [32] which involved student surveys, group discussions, input from school staff, and observational notes. Modifications were made based on the feedback, addressing technical difficulties, adding group discussion opportunities, including physical activity and removing unpopular activities like pledges to remain e-cigarette free. Schools indicated a preference for a ‘flexible implementation’ approach to ensure alignment with school priorities which would allow schools to implement the 2 × 60 min peer-education lessons back-to-back or over the course of two weeks.

### Study design

This is a pre-post study seeking to change perceptions and behaviours of Year 7 and 10 students, with outcomes assessed both quantitatively and qualitatively. Students will complete surveys prior to and four-weeks after baseline to evaluate changes in knowledge, perceptions, refusal skills and intentions to use e-cigarettes. Mixed methods research generates rich insights about the conditions required for the successful adoption, implementation and maintenance of interventions [33]. The study has received ethics approval from the University of Sydney Human Research Ethics Committee (2024/HE000200).

### Sample size

This study aims to evaluate the effect of the BEAT program on knowledge, attitudes towards, and usage of e-cigarettes. The primary outcome variable measures the within subject change from pre- to post-intervention for students past 30-day e-cigarette use. At least 12 schools will participate with each school considered as a ‘cluster’. Within each school two cohorts of students, namely ‘Year 10 Peer Leaders’ and ‘Year 7 students’ will be studied. Based on past experience, it is expected that at least 15 Peer leaders and 100 Year 7 students at each school will complete the questionnaire both pre- and post-intervention.

### Power analysis

Each cohort will be considered separately. In order to maintain an overall 5% two-sided significance level, the null hypothesis of no change for the primary outcome variable across two time points will be tested using a paired Wilcoxon signed-rank test accounting for potential non-normality of the outcome. Given the naturally clustered data (e.g., students clustered within schools), the smallest detectable effect size is based on the “effective sample size” that was calculated by adjusting the proposed sample size by the study design effect. Assuming cohort sample sizes of 180 ‘Year 10 Peer Leaders’ (15 leaders per school) and 1200 ‘Year 7 students’ (100 students per schools), the study will have at least 80% power to detect the effect sizes for various intraclass correlation coefficients (ICC) ranging from 0.01 to 0.05. The minimal detectable effect sizes for the Year 10 Peer Leaders range between 0.230—0.281, whereas the minimal detectable effect sizes for the year 7 students range between 0.117—0.203 (see Table 2). All power calculations were conducted using G*Power 3.1.9.7.

**Table 2 Tab2:** Range of detectable effect sizes in students

ICC	Cohort							
	**Year 10 peer leaders (*****n***** = 12*15 = 180)**				**Year 7 students (*****n***** = 12*100 = 1200)**			
	**m**	**DE**	**n/DE**	**Effect size required#**	**m = 100**	**DE**	**n/DE**	**Effect size required#**
0.01	15	1.14	158	0.230	100	1.99	603	0.117
0.02	15	1.28	141	0.243	100	2.98	403	0.143
0.03	15	1.42	127	0.256	100	3.97	302	0.166
0.04	15	1.56	115	0.270	100	4.96	242	0.185
0.05	15	1.7	106	0.281	100	5.95	202	0.203

^*#*^* Smallest Effect size detectable with 80% power*

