### Effectiveness

#### Primary outcome

The primary outcome is change in past-30-day e-cigarette use reported among students. This will be assessed by asking ‘During the last 30 days, on about how many days did you vape?’ with response choices ranging from 0 to 30 days. The primary endpoint will be assessed at four weeks from baseline, post-intervention.

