## Analysis

### Statistical analysis

Data collected will be non-identifiable, cleaned and imported into the R software environment for statistical computing. Participants’ unique ID number will be used to match data from the two time points. Descriptive statistics and changes between data collection points will be assessed for statistical significance (P < 0.05). Wilcoxon signed rank tests (a non-parametric alternative for paired t-tests, pairs are within subject’s pre and post survey responses) will be used for within-subject comparisons. Cluster-robust standard errors will be implemented using the ‘clusrank’ R package [52]. To assess if students who are excluded from analysis (e.g., pre-survey could not be linked to a post-survey using the identifying code) are substantively different from those included in our analysis, we will quantify the comparability between the unlinked and linked participants using standardized mean differences (SMDs) of key pre-test study variables. We will interpret standardized mean differences values of > 0.20 to be large differences between groups. Sensitivity analysis will use multiple imputation to explore the impact of missing data on study results.

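### The plan claims an overall 5% significance level, but tests the primary outcome at 5% in each of two cohorts and states no rule that controls error across them

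*Protocol article*

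**What the plan says.** The Sample size section of the protocol article sets up two groups: "Within each school two cohorts of students, namely ‘Year 10 Peer Leaders’ and ‘Year 7 students’ will be studied". The Primary outcome section defines one endpoint for both: "The primary outcome is change in past-30-day e-cigarette use reported among students". It does not say which cohort leads. The study objectives at the end of the Background name impact in both year groups.

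The Power analysis section says "Each cohort will be considered separately. In order to maintain an overall 5% two-sided significance level", and continues that the null hypothesis of no change "will be tested using a paired Wilcoxon signed-rank test accounting for potential non-normality of the outcome". Table 2 then gives the smallest effect detectable with 80% power in each cohort, for ICCs of 0.01 to 0.05. The alpha behind the table is not printed beside it.

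The Statistical analysis section gives a general threshold: "changes between data collection points will be assessed for statistical significance (P < 0.05"). The article mentions no division of alpha, no testing order, and no requirement that both cohorts succeed.

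**The concern.** An overall significance level is a statement about the set of primary tests taken together. Here there are two, and the sentence offers the choice of a Wilcoxon test as the way to hold the level. That choice protects a single test against non-normality. It does not limit the chance that at least one of two tests is falsely significant.

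The Discussion makes funding for wider dissemination depend on the program being effective, and the article does not say how two cohort results combine into that judgement. If one cohort is significant and the other is not, the stated error rate would describe the conclusion only if some linking rule were in force.

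**Working it through.** **Inputs.** Power analysis section and Table 2: 12 schools; cluster sizes m = 15 (Year 10, n = 180) and m = 100 (Year 7, n = 1200); ICC 0.01 to 0.05; 80% power; two-sided test; matched-pairs Wilcoxon signed-rank test in G*Power.

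**Step 1: effective sample size.** Design effect DE = 1 + (m − 1) × ICC. At ICC 0.01:
- Year 10: 1 + 14 × 0.01 = 1.14, and 180 / 1.14 = 157.9, printed as 158.
- Year 7: 1 + 99 × 0.01 = 1.99, and 1200 / 1.99 = 603.0, printed as 603.

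The other rows agree in the same way.

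**Step 2: which alpha does Table 2 use?** For a signed-rank test with a normal parent distribution, set N = (n/DE) × 3/π, with N − 1 degrees of freedom and noncentrality d√N. Solve the noncentral t distribution for the d that gives 80% power.

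| ICC | Year 10 printed | α = 0.05 | α = 0.025 | Year 7 printed | α = 0.05 | α = 0.025 |
|---|---|---|---|---|---|---|
| 0.01 | 0.230 | 0.2296 | 0.2531 | 0.117 | 0.1169 | 0.1288 |
| 0.02 | 0.243 | 0.2432 | 0.2682 | 0.143 | 0.1432 | 0.1577 |
| 0.03 | 0.256 | 0.2565 | 0.2829 | 0.166 | 0.1655 | 0.1823 |
| 0.04 | 0.270 | 0.2697 | 0.2976 | 0.185 | 0.1851 | 0.2039 |
| 0.05 | 0.281 | 0.2812 | 0.3103 | 0.203 | 0.2027 | 0.2234 |

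All ten printed values agree to within 0.001 at two-sided 0.05 per cohort, and none agrees at two-sided 0.025. (A one-sided 0.025 test would give the same figures as a two-sided 0.05 test, but the article says two-sided.) So the table contains no division of alpha.

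**Step 3: error across the two cohorts with no linking rule.**
- Independent tests: 1 − 0.95² = 0.0975.
- Upper bound under any dependence: 0.05 + 0.05 = 0.10.
- Correlated test statistics (bivariate normal, correlation r assumed because the article gives none): 9.7% at r = 0.1, 9.5% at r = 0.3, 9.1% at r = 0.5, 7.8% at r = 0.8.

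**Step 4: cost of holding 5% across cohorts at 0.025 each.** The error rate becomes 1 − 0.975² = 4.94% if independent, and at most 5%. Detectable effects at 80% power become 0.253–0.310 (Year 10) and 0.129–0.223 (Year 7), about 10% larger than printed (for example 0.253 / 0.230 = 1.10). Power at the printed effect sizes falls from about 80% to between 70.8% and 71.4%.

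**The case against.** The best counter-argument lies in the text itself. The sentence just before the claim separates the cohorts, and the next speaks of a single null hypothesis. The cohorts also receive different things: Year 10 students take a one-day workshop and deliver lessons, while Year 7 students receive two lessons. Treating them as two questions, each at 5%, is defensible and needs no adjustment. This stands as a possible reading, but *overall* is then the wrong word.

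A reader might infer from Table 2 that error across cohorts has been shown to be uncontrolled. It has not. A fixed sequence or a both-must-succeed rule would also use 5% in each test, so the match rules out only a division of alpha. The threshold in the Statistical analysis section is general and does not say how the two primary tests combine. A condensed article may also leave such a rule to a fuller document. The point therefore rests on what the article asserts: an overall level, credited to a test that cannot deliver it.

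A reader might also infer that significance in either cohort will be declared a positive study. No section says so.

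Finally, a reader might conclude that Year 7 must be tested first because the program is preventive. The objectives and the Study design section target both years, and the only Australian past-30-day prevalence quoted (14.5% in 2023) is for ages 14–17. If use is low at 11–13, which is an assumption, placing Year 7 first could block the cohort with more room to change.

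**Conclusion.** The concern holds as a defect in the stated error rate. On the across-cohort reading, the procedure as described gives 9.75% under independence and at most 10%, against the claimed 5%. Some correlation through shared schools would lower this, but it stays at 7.8% even at an assumed correlation of 0.8. On the per-cohort reading the tests are acceptable and the wording is not. The sentence needs correcting either way.

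These figures assume that both nulls are true, that each test holds its own 5% level, and that no unstated rule links the tests. The documents do not support saying that the investigators intended overall control and breached it. Severity is minor to moderate: no sample size, data collection or choice of test has to change, and this is an uncontrolled pre-post evaluation.

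**What to change.** Choose one of the following before the data are analysed.

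1. **Keep 5% overall.** Apply Holm to the two primary tests: the smaller P value is compared with 0.025 and, if that is significant, the larger with 0.05. Restate Table 2 at alpha 0.025, using the last column for each cohort in the table above. This is slightly conservative, since under Holm the second test may use 0.05. The cost is detectable effects about 10% larger.
2. **Claim less.** Replace the overall 5% claim with 5% per cohort and no control across cohorts. Report Year 10 and Year 7 as separate questions, and do not present one significant cohort as evidence that the program as a whole is effective. The cost is a more modest error-rate claim; Table 2 stands.

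A fixed sequence at 5% per step would also make the overall claim true. Which cohort goes first is the investigators' choice and should be justified in the text. Its cost falls on the second cohort: if the tests are independent and both effects are exactly at the printed sizes, its chance of success is 0.80 × 0.80 = 64%.

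Each option is a sentence or two in the Power analysis and Statistical analysis sections, plus a revised Table 2 under option 1.

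### Table 2's claim of at least 80% power treats n/DE as independent students; with 12 schools, a test that holds 5% has about 72–73% power

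*Protocol article*

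**What the plan says.** - **Clusters and numbers (Sample size).** "At least 12 schools will participate with each school considered as a" cluster, and it is expected that "at least 15 Peer leaders and 100 Year 7 students at each school will complete the questionnaire both pre- and post-intervention".
- **Test and level (Power analysis).** The aim is stated as "In order to maintain an overall 5% two-sided significance level". For each cohort separately, the absence of any pre-post change in the primary outcome "will be tested using a paired Wilcoxon signed-rank test accounting for potential non-normality of the outcome".
- **Allowance for clustering (Power analysis).** Detectable effects rest on an effective sample size "that was calculated by adjusting the proposed sample size by the study design effect". Table 2 does this for exactly 12 × 15 = 180 and 12 × 100 = 1200 students, using G*Power.
- **Claim (Power analysis).** "the study will have at least 80% power to detect the effect sizes for various intraclass correlation coefficients (ICC) ranging from 0.01 to 0.05". Table 2 puts the detectable effects at 0.230 to 0.281 for Year 10 and 0.117 to 0.203 for Year 7.
- **Planned analysis (Statistical analysis).** Within-student signed-rank tests. "Cluster-robust standard errors will be implemented using the" clusrank R package. No reference distribution or degrees of freedom are stated.

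**The concern.** Clustering affects a test in two ways. It inflates the variance of the estimate, and the design effect deals with that. It also limits how well the variance can be known: a cluster-robust variance is built from between-school variation, so its precision depends on the number of schools, whatever the ICC and however many students each school supplies. Table 2 handles the first effect only. Its reference distribution has roughly 100 to 575 degrees of freedom, where the design supplies 11.

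If the error rate is held at 5%, the chance of missing an effect of the tabulated size is about 27–28%, not 20%, and a null result would be read as stronger evidence than it is. If a large-sample reference is used instead, the false-positive rate rises to about half as much again as promised. This is an uncontrolled pre-post study, and the Discussion ties a favourable result to seeking funds for dissemination.

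**Working it through.** **Inputs (Sample size, Power analysis and Table 2).** K = 12 schools; m = 15 (Year 10) or 100 (Year 7) completers per school; ICC 0.01–0.05; two-sided 5%; effect size d = mean change divided by SD of change.

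**Step 1: reproduce Table 2.** DE = 1 + (m − 1) × ICC. Year 10 at ICC 0.05: 1 + 14 × 0.05 = 1.70, and 180/1.70 = 106. Year 7 at ICC 0.05: 1 + 99 × 0.05 = 5.95, and 1200/5.95 = 202. All ten DE and n/DE values agree with the table.

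The usual normal-parent approximation for the signed-rank test sets n′ = (n/DE) × 3/π (relative efficiency 0.955), with noncentral t, df = n′ − 1 and noncentrality d√n′. It returns every tabulated effect size to within 0.001, with power of 79.9–80.2% at the tabulated values. So this is the method used, and it was applied correctly. A plain paired t or a relative efficiency of 0.864 does not match the table.

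**Step 2: keep the noncentrality and use the degrees of freedom that 12 schools give.** df = 12 − 1 = 11, so the critical value is 2.201. Example, Year 10 at ICC 0.05: n′ = 106 × 3/π = 101.2; noncentrality = 0.281 × √101.2 = 2.83; power = 73.1%. With 11 df, 80% power needs a noncentrality of 3.078, so the detectable effect is 3.078/√n′ = 3.078/10.06 = 0.306.

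| Cohort | ICC | n/DE | Stated effect | Power, 11 df | Effect for 80%, 11 df |
|---|---|---|---|---|---|
| Year 10 | 0.01 | 158 | 0.230 | 73.0% | 0.251 |
| | 0.02 | 141 | 0.243 | 72.8% | 0.265 |
| | 0.03 | 127 | 0.256 | 72.8% | 0.280 |
| | 0.04 | 115 | 0.270 | 73.1% | 0.294 |
| | 0.05 | 106 | 0.281 | 73.1% | 0.306 |
| Year 7 | 0.01 | 603 | 0.117 | 72.5% | 0.128 |
| | 0.02 | 403 | 0.143 | 72.4% | 0.157 |
| | 0.03 | 302 | 0.166 | 72.8% | 0.181 |
| | 0.04 | 242 | 0.185 | 72.6% | 0.203 |
| | 0.05 | 202 | 0.203 | 72.8% | 0.222 |

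The table uses n/DE rounded as in Table 2. Unrounded values move a few entries by 0.001 or 0.1 percentage point.

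**Step 3: check by simulation.** Twelve equal schools and normally distributed changes; T = a school's sum of signed ranks; 3000–4000 runs per scenario.

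| Version of the clustered signed-rank test | Power at stated effect | Type I error |
|---|---|---|
| ΣT/√ΣT² with normal reference | 71–73% | 4–5% |
| Centred between-school variance, t with 11 df | 73–75% | 5–5.5% |
| School-level sign-flip permutation | 73–74% | 4–6% |
| Centred between-school variance, normal reference | 80–82% | 7–8% |

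Theory agrees with the last row: P(|t₁₁| > 1.96) = 7.6%.

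**The case against.** - **The arithmetic is right on its own method.** This stands. Every entry in Table 2 reproduces and the method is disclosed. The fault is that the method does not match the planned cluster-adjusted test.
- **The protocol names no reference distribution, so 72% is not a fixed fact.** This is right in part. How the package forms its variance and P value is not stated, and the 11-df figure is a calculation for a test that holds its level. But the conclusion survives the uncertainty: each version near 5% gives about 71–75% power, and the only one reaching 80% exceeds the promised level. Leaving the choice of reference to an analysis plan would not rescue a power figure already published.
- **12, 15 and 100 are minimums.** Also true. The Intervention section expects about 15–30 peer leaders per school. With 12 schools and 20 completing leaders each, Year 10 power at the stated effects would be 79–83%; with 150 Year 7 completers per school, Year 7 power would be 75–80%. However, the 15–30 counts participants rather than completers, and both Table 2 and the 80% claim are made for exactly 12, 15 and 100.
- **The practical change is small.** A shift of 9–10% in detectable effect is less than the spread across the ICC range (0.230 to 0.281, or 22%, in Year 10; 0.117 to 0.203, or 74%, in Year 7), and no target effect is named. That limits the seriousness of the point, but a stated power figure should still be correct.
- **The corrected values are also normal-theory values.** Correct. Days vaped will probably show many zero changes, and schools will differ in size. Neither was quantified.

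**Conclusion.** The concern holds. At 12 schools with 15 or 100 completers each, power at the Table 2 effect sizes is about 72–73% when the variance is estimated with 11 degrees of freedom. Simulated tests with type I error near 5% give 71–75%. The stated pair of 5% and at least 80% is not delivered in any row. The effects detectable with 80% power are 0.251–0.306 (Year 10) and 0.128–0.222 (Year 7), about 9–10% above the stated values.

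These figures assume equal school sizes, normally distributed changes and the ICCs in the table. The point is a misstated power figure for the primary outcome that should be corrected; it does not invalidate the design.

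**What to change.** 1. **Restate Table 2 on 11 degrees of freedom**, and say so in its footnote. For ICC 0.01 to 0.05, Year 10: 0.251, 0.265, 0.280, 0.294, 0.306. Year 7: 0.128, 0.157, 0.181, 0.203, 0.222. Change the ranges in the Power analysis text to match, and state the assumptions of equal school sizes and normal changes.
2. **Name the reference distribution for the primary test** in the Statistical analysis section. A school-level sign-flip permutation of the rank totals (2¹² = 4096 sign patterns) suits 12 schools and held about 5% in simulation. Another reference shown to hold 5% with 12 clusters would also do; a centred cluster variance with a normal reference would not.

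The cost is one table and a sentence or two, with slightly less favourable stated effects. No extra schools or data are needed. If the sponsor would rather keep the present effect sizes at 80% power, about 14 schools of the same size would be required (15 for the Year 7 row at ICC 0.02, where 14 gives 79.9%).
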